# Monitoring the clinical practice of palliative sedation (PALSED) in patients with advanced cancer: an international, multicentre, non-experimental prospective observational study protocol

**DOI:** 10.1186/s12904-022-01125-w

**Published:** 2023-01-28

**Keywords:** Palliative sedation, Observational study, End of life care, Advanced Cancer, Monitoring

## Abstract

**Background:**

Palliative sedation involves the intentional lowering of consciousness at the end of life. It can be initiated to relieve a patient’s burden caused by refractory symptoms at the end of life. The impact of palliative sedation needs to be clinically monitored to adjust the proper dose and regimen of sedative medication to ensure that patients are at ease and comfortable at the end of their lives. Although there is consensus among health care professionals and within guidelines that efficacy of palliative sedation needs to be closely monitored, there is no agreement about how, when, and by whom, this monitoring should be performed. The aim of this study is to evaluate the effects of palliative sedation by measuring the discomfort levels and sedation/agitation levels of the patients at regular timepoints. In addition, the clinical trajectories of those patients receiving palliative sedation will be monitored and recorded.

**Methods:**

The study is an international prospective non-experimental observational multicentre study. Patients are recruited from in-patient palliative care settings in Belgium, Germany, Italy, Spain and the Netherlands. Adult patients with advanced cancer are monitored by using proxy observations of discomfort (DS-DAT) and depth of sedation/agitation levels (RASS-PAL) during palliative sedation. After the palliative sedation period, the care for the specific participant case is evaluated by one of the attending health care professionals and one relative via a questionnaire.

**Discussion:**

This study will be the first international prospective multicenter study evaluating the clinical practice of palliative sedation including observations of discomfort levels and levels of sedation. It will provide valuable information about the practice of palliative sedation in European countries in terminally ill cancer patients. Results from this study will facilitate the formulation of recommendations for clinical practice on how to improve monitoring and comfort in patients receiving palliative sedation.

**Trial registration:**

This study is registered at Clinicaltrials.gov since January 22, 2021, registration number: NCT04719702.

## Background

An increase in cancer incidence together with a longer survival time for patients with advanced cancer is observed. Increasing treatment possibilities are available but are accompanied with progressively more morbidity. Therefore, the number of patients in need for end-of-life care is likely to increase [1]. Patients with advanced cancer may experience symptoms due to metastatic disease, but also due to treatment related side effects that significantly influence their quality of life such as pain, delirium or dyspnea [2]. For most terminally ill patients, these symptoms can be controlled towards the end of life with conventional treatment strategies. However, in some patients the symptom burden persists despite optimal treatments, resulting in ‘refractory symptoms’ [3]. For these patients with intolerable suffering and a limited life expectancy, palliative sedation may be indicated. This involves the intentional lowering of consciousness at the end of life, to relieve a patient’s perception of suffering [4]. The intensity of palliative sedation can vary in terms of the level of sedation, which can be mild, intermediate or deep, and the type of the sedation which can be intermittent or continuous [5]. Reported incidence of palliative sedation varies greatly between countries and between individual care settings. In some European countries the use of palliative sedation, mainly continuous deep sedation, has been studied [6, 7]. In these studies, the reported use of continuous deep sedation in patients with a palliative care need in different palliative care settings varies between 2.5% (Denmark) and 18.3% (The Netherlands) [7].

Most guidelines recommend that the level of palliative sedation should be proportional to the intended clinical effect of symptom relief [8]. Previous studies demonstrated a large variation of clinical evaluation methodologies to monitor the clinical efficacy of palliative sedation [9, 10]. Additionally, close monitoring of discomfort during palliative sedation is rare [11, 12].

Moreover, major differences between study protocols and characteristics occur, for instance in patient characteristics, definition of palliative sedation, and its indication to start. Consequently, reported outcomes and associated treatment goals differ between these studies which prevent the generalization of outcomes and decisions about the effective use of palliative sedation in clinical practice [10].

To understand the observed clinical outcomes of palliative sedation in patients with cancer suffering from refractory symptoms, it is important to relate these to the reasons to start palliative sedation, the prescribed drugs and dosages and the specific clinical context where they are measured. Moreover, differences across various palliative care settings and European countries in both clinical and ethical aspects should be included in the interpretation of the results [13]. So far, multinational clinical research for this purpose is lacking. Hence, there is an urgent need for internationally and prospectively observational standardized research on palliative sedation.

To study the clinical practice and outcomes of palliative sedation from different perspectives, we conducted a prospective multicenter non-experimental observational study in cancer patients from palliative care settings, in five European countries.

### The primary objective of this study is

To evaluate the effects of palliative sedation on advanced cancer patient’s comfort levels in hospices, palliative care units and hospital wards in five European countries.

### Secondary objectives

To evaluate the effects of palliative sedation on patient’s sedation levels in hospices, palliative care units and hospital wards in five European countries.To describe the current clinical practice of palliative sedation in hospices, palliative care units and hospital wards in five European countries.To describe the evaluations of the relatives and health care professionals with the palliative sedation given in the patient cases.

## Methods

### Design

In this clinical observational study, participants with advanced and untreatable cancer will be followed prospectively after informed consent given prior to the start of the decision-making process for end-of-life care until death. Before and during the palliative sedation in a patient, prospective measures and clinical observations will be performed to evaluate the sedation process. After the patients’ death, one of the attending health care professionals and one of the relatives will receive a questionnaire to evaluate the palliative sedation and care in the specific patient case.

### Participating settings

This prospective study will be conducted in five European countries: Belgium; Germany; Italy; Spain and the Netherlands. Participants are recruited from in-patient palliative care settings: hospital wards; palliative care units and hospices. In each country, we are aiming to recruit 30 participants receiving palliative sedation.

### Sample size calculation

In the study by van Deijck and colleagues [11] a mean difference of 4 points was found in comfort levels measured with the DS-DAT before and after the start of palliative sedation.

Because the present study will aim to include a wider range of settings and with more variability in forms of palliative sedation, therefore the effects may be smaller. Estimating a smaller effect size of 2.4 points on the DS-DAT, using an alpha of 0.05 and 0.80 power in a two-sided, paired t-test, with a standard deviation of 6.2, and correcting for clustering due to the multiple international centre settings (using an ICC of 0.05 and pre-assumed design effect of 1.2) we will need to include 110 sedated patients. To anticipate at missing data and dropout rate during the study we aim to include 150 sedated patients in total.

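### The 110 sedated patients do not follow from the stated inputs, which give 66; the document does not show which input is misreported

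*Protocol article*

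**What the plan says.** All the inputs are in the Sample size calculation section of the protocol article:

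- Test, error rate and power: "using an alpha of 0.05 and 0.80 power in a two-sided, paired t-test".
- Difference: "Estimating a smaller effect size of 2.4 points on the DS-DAT".
- Variability: "with a standard deviation of 6.2". The text does not say whether this is the SD of the before-after change or of a single score.
- Clustering and result: "using an ICC of 0.05 and pre-assumed design effect of 1.2) we will need to include 110 sedated patients". The correction is attributed to the several international centres. No cluster size or number of clusters is given.
- Allowance for losses, applied after that result: "To anticipate at missing data and dropout rate during the study we aim to include 150 sedated patients in total".

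The Participating settings section gives the split of the target: "In each country, we are aiming to recruit 30 participants receiving palliative sedation". Over five countries this is 5 x 30 = 150, which agrees with the total.

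**The concern.** This is the planning number for the primary outcome, and the paragraph gives every quantity needed to check it. The result is well above what those quantities produce, by more than rounding or a choice of approximation can explain. The loss allowance cannot explain it either, because it is applied only in the step from 110 to 150.

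What is at stake is the meaning of 110. The Limitations section expects missing measurements when sedation has to start quickly, so the number of evaluable patients may fall below target. A reader should then be able to tell whether the minimum for 80% power is 66, 110 or some other number, and which clustering the study was planned to absorb. The paragraph as printed does not allow that.

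**Working it through.** **Inputs** (Sample size calculation): difference 2.4; SD 6.2; two-sided alpha 0.05; power 0.80; ICC 0.05; design effect 1.2.

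**Step 1: attempt to reproduce 110.**

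- Normal approximation: n = ((1.960 + 0.842) x 6.2 / 2.4)^2 = 52.4, so 53. With clustering, 53 x 1.2 = 63.6, so 64.
- Exact noncentral t, standardised difference 2.4 / 6.2 = 0.387: n = 54 gives 79.7% power and n = 55 gives 80.5%, so 55. With clustering, 55 x 1.2 = 66.
- The stated 110 is not reproduced. The excess is 110 - 66 = 44, and 44 / 66 = 67%.

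**Step 2: which single change would give about 110, other inputs held.**

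| Input changed | Value needed | Result |
|---|---|---|
| Design effect | 110 / 55 = 2.0 | 55 x 2.0 = 110 |
| SD of change | about 8.1 | 110 at design effect 1.2 |
| Power | 0.95 | 89 x 1.2 = 106.8, so 107 |
| Difference | about 1.83 | 110 at design effect 1.2 |

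The SD row has a plausible route. If 6.2 is the SD of a single score and the before-after correlation is r, the SD of change is 6.2 x sqrt(2(1 - r)). With r = 0.15 (an assumption; the article gives no correlation) this is 8.08, which needs 91 patients, and 91 x 1.2 = 109.2. With r = 0.5 it is 6.2 again, and the answer returns to 66.

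**Step 3: what the ICC and design effect imply.** Design effect = 1 + (m - 1) x 0.05, where m is patients per cluster:

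- m = 5: 1.20
- m = 21: 2.00
- m = 22 (110 over five countries): 2.05
- m = 30 (150 over five countries): 2.45

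**Step 4: power by reading**, with SD of change 6.2, difference 2.4 and effective n = N / design effect:

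| N evaluable | Clustering | Design effect | Effective n | Power |
|---|---|---|---|---|
| 110 | as printed | 1.2 | 91.7 | 95.6% |
| 110 | value that closes the sum | 2.0 | 55.0 | 80.5% |
| 110 | by country, 22 each | 2.05 | 53.7 | 79.5% |
| 150 | as printed | 1.2 | 125.0 | 99.0% |
| 150 | by country, 30 each | 2.45 | 61.2 | 84.6% |

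**The case against.** The best defence is that the paragraph may be a correct calculation reported incompletely. If 6.2 is a single-score SD and the correlation is low, 110 follows with the design effect of 1.2 intact. The clustering inputs also agree with each other: ICC 0.05 and design effect 1.2 fit about five patients per centre, and the text attributes the clustering to centres. This part stands, and it limits what can be concluded. It does not rescue the paragraph, because the SD, correlation or power that would make 110 correct is not the one a reader finds there. A loss allowance already folded into 110 is also arithmetically possible (66 / 0.6 = 110, a 40% loss), but the text adds its allowance afterwards.

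A reader might infer three stronger things, none of which the document supports:

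- *The design effect is the wrong input and should be 2.0.* 55 x 2.0 = 110 is suggestive, and 2.0 is close to country-level clustering. It is still one of several single changes that close the sum, and country as the cluster is only one reading.
- *The stated power is wrong.* The 0.80 is a design target. If the design effect really is 2.0, 110 patients have 80.5%, as intended. If every printed input is right, they have about 96%.
- *The study falls clearly short of 80%.* Applying the design effect of 2.45 to 110 patients gives about 72%, but that value needs 30 patients per country, which is 150 patients. With 110 patients over five countries the design effect is 2.05 and the shortfall is half a percentage point.

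On the printed inputs the discrepancy is also in the conservative direction.

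**Conclusion.** The point holds as an arithmetic inconsistency in the planning number for the primary outcome. The printed inputs give 66 patients (64 by the normal approximation), not 110, so at least one of the SD, difference, design effect, power or total is misreported. The article does not show which.

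Depending on the reading, 110 evaluable patients have about 79.5% power (clustering by country, 22 each) to about 96% (as printed). With 150 evaluable patients the power is at least about 85% under the design effects considered, so the recruitment target is not shown to be too small.

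These power figures assume that 6.2 is the SD of the paired change, that the true difference is 2.4 and that the ICC is 0.05. The country-level figures further assume equal numbers per country.

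**What to change.** Restate the paragraph from the inputs actually used, so that it closes:

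- Say whether 6.2 is the SD of the paired change. If it is the SD of a single score, give the before-after correlation used.
- Name the cluster unit (centre or country) and its expected size m, and derive the design effect as 1 + (m - 1) x 0.05.
- Show the unadjusted number, the design effect and their product, and then the loss rate that leads to 150. Going from 150 to 110 implies 1 - 110/150 = 26.7%, which is not stated.
- If the printed inputs stand, give 66 as the required number and report about 96% power at 110 evaluable patients.

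Do not choose a design effect because it returns 110; the cluster unit and size should determine it. The cost is one rewritten paragraph. No extra patients are needed and the target of 150 can stay.

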### Study population

All adult patients with a diagnosis of advanced cancer and a limited life expectancy, as assessed by the attending health care professionals, are eligible for inclusion. Additionally, intractable distress caused by one or more symptoms during the hospitalization needs to be present or expected, according to the health care team. Lastly, patients need to be able to give informed consent (see Table 1).

For the included patients, data are collected only during admission to one of the participating settings. For patients who are discharged alive or die without palliative sedation, data collection and study participation ends.

In each patient case that will be monitored during palliative sedation, the following persons will be invited to participate by completing an evaluation questionnaire after the palliative sedation period: 1) one of the health care professionals (physician or nurse) involved in the initiation of palliative sedation; 2) one of the relatives, who takes care of, and supports, the patient for most of the time. This relative may not necessarily be a family member.

**Table 1 Tab1:** Inclusion- and exclusion criteria

**Inclusion criteria:** Patients are eligible for inclusion If they are;	•18 years or older; •diagnosed with advanced cancer; •having a limited life expectancy; •suffering from intractable distress caused by one or more refractory symptoms or this can be expected to develop during the hospitalization; •having the possibility that palliative sedation will be initiated during the admission •able to give informed consent.
**Exclusion criteria:** Patients are excluded for participation in the study if;	•a potential participant is unable to speak and read in the native language of the participating country.

### Recruitment

All consecutively admitted patients in the participating settings will be screened for eligibility by a health care professional from the local participating setting. Eligible patients and their relative(s) will be informed by the responsible health care team about this study as soon as possible after admission. This team defines in each particular case what is the best timing to ask for informed consent.

Screening and recruitment for the study started May 2021, and will be in progress for 24 months.

### Study procedures

Potential participants receive the information letter via one of the responsible health care professionals in the participating setting. When a potential participant has had sufficient time to consider and indicate that he/she would like to know more about participating, the local researcher is notified. One of the local researchers will visit the patient to explain the study, answer questions and discuss participation. Preferably, the informed consent procedure is performed by one of the local researchers independent of the patient’s care team. In addition, at each clinical centre, there is a local principal investigator that serves as a primary contact point for the study or to perform the informed consent procedure. Informed consent is requested for obtaining data about the patient’s treatment trajectory following admission.

### Study outcomes

The main outcome of this study is the proxy measurement of change in discomfort levels of patients before and during the period they receive palliative sedation.

As a secondary outcome, proxy measurement of agitation/sedation levels will be measured at the same time points as the discomfort levels, to evaluate a correlation in the course of both measurements.

Other outcomes in this study are clinical aspects in the process of decision-making about palliative sedation; administered type, doses of sedative medication and adverse effects as reported in the patients notes and in the case report forms. Besides, one of the health care professionals completes a questionnaire regarding the overall evaluation of palliative sedation in the specific patient case. Lastly, one of the relatives is asked to rate how satisfied he/she was with the care for the patient during the palliative sedation period.

### Data collection

Data collection is planned to use a two-stage approach (See Fig. 1). When informed consent is gained, baseline information for all patients is collected for phase 1. Then study measurements are paused and participants are clinically followed by the health care team.

**Fig. 1 Fig1:**
[figure not shown]
Study flow phase 1 and phase 2. All study participants start in phase 1 of the study, and participants in which the decision making is started regarding palliative sedation enter phase 2 of the study, all participants reaching the end of study due withdrawal consent, discharge or decease

Only those patients in which the process for palliative sedation is initiated will advance to phase 2 of the study. In this phase, extra questionnaires and measurements are completed by the health care professionals at the bedside, regarding the decision-making process of palliative sedation, baseline discomfort levels, the use of medication and other clinical aspects of palliative sedation.

To gather data about the study parameters we predominantly use data that is normally collected in clinical practice at the participating settings. This data is gathered from the available patient data management system (PDMS), and directly registered into the electronic case report form. Required study data regarding baseline measurements and all palliative sedation measurements, not regularly registered in the PDMS, are collected by study questionnaires or measured by additional scales.

Assessment of variables is planned at different time points during the trajectories of the study participants, and contains more measurements for the participants who start with palliative sedation (See Fig. 2).

**Fig. 2 Fig2:**
[figure not shown]
Study timeline and assessments. The measurements and questionnaires are completed at different time points during the trajectories of the study participants, For the participants who start with palliative sedation more assessments are planned

### Baseline measurements

#### Symptom burden

The Edmonton Symptom Assessment System (ESAS) is an assessment scale designed to assess the symptom burden of the patient. It contains 9 items, scored on a visual analogue scale [14]. As baseline measurement, all participants are asked to complete the Edmonton Symptom Assessment System (ESAS) after inclusion in the study. A second measurement will be done before initiation of palliative sedation by the patient themselves if possible or as a proxy measurement by the health care professional.

#### Performance Status

The Eastern Cooperative Oncology Group (ECOG) Performance Status is a scale that uses standard criteria to measure the impact of the disease on patient’s daily living abilities. The scale describes a patient’s level of functioning in terms of their ability to care for themself, conduct daily activities, and physical ability [15]. The ECOG performance score is completed by one of the attending physicians or clinical researchers as a baseline measurement in this study.

### Outcome measurements during palliative sedation

#### Monitoring comfort

The Discomfort Scale-Dementia of Alzheimer Type (DS-DAT) is a validated instrument to assess discomfort in patients with severe dementia by observing patients’ behavior over 5 minutes of observation. Participating health care teams were trained online and at bedside how to use the DS-DAT tool. The tool covers nine categories: noisy breathing, negative vocalizations, content facial expression, sad facial expression, frightened facial expression, frown, relaxed body language, tense body language, and fidgeting. Items are scored by indicating behaviors that are present/absent with a resulting range of scores of 0 to 3 per item and a total score from 0 to 27. Higher scores represent higher amount of discomfort [16].

In our study the DS-DAT is measured 8 hours or less before the start of palliative sedation, within 6 hours after the start, and then twice daily during the period palliative sedation is provided by one of the attending health care professionals.

#### Depth of sedation

The Richmond Agitation Distress Scale-modified version for Palliative care (RASS-PAL) is an observational instrument assessing levels of sedation and agitation that requires no patient input with scores ranging from + 4 (overtly combative patient) to − 5 (no arousal by either voice or physical stimulation) [17].

The depth of sedation as assessed with the RASS-PAL will be measured at the same time points as the discomfort measurements.

